**Objective:**

The main aim of this study is to compare the efficacy of an added mirror therapy component with fNMR in patients with peripheral facial palsy (PFP) sequelae in 3 different stages. The specific objectives of this study are to measure the effects of combined therapy compared to fNMR alone on (1) participants’ facial symmetry and synkinesis, (2) quality of life and psychological aspects of the participants, (3) motivation and treatment adherence, and (4) different stages of facial palsies.

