### Study Aims

There is a growing interest in exploring the effect of adding mirror therapy as a biofeedback tool in fNMR, particularly in patients with peripheral facial palsy dealing with sequelae 3-12 months after onset. Therefore, the general aim of this protocol is to compare the potential effects of adjunctive mirror therapy with the gold standard fNMR on facial function and rehabilitation in nonflaccid facial paralysis. The specific objectives of this study are (1) to measure the effects of combined therapy compared to fNMR alone on participants’ facial symmetry and facial synkinesis, (2) to measure the effects of combined therapy versus fNMR alone on the quality of life and psychological aspects of the participants, and (3) to measure the effects of combined therapy versus fNMR alone on motivation and treatment adherence.

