### Recruitment and Compensation

As determined, thanks to a power calculation measure based on Martineau et al [22] to reach a power of 0.8 with a size effect of 0.6 and an α of .005, 90 patients with peripheral facial palsy of diverse etiologies in the paretic (n=30), early synkinetic (n=30), or chronic synkinetic phase (n=30) will be recruited to the study. They will then be randomized into 2 groups, mirror therapy plus fNMR or fNMR alone, by computerized block randomization. No compensation or incentive is planned to be provided at this time. Recruitment is planned to be conducted in 3 tertiary care centers (hospitals) in Canada, England, and Belgium (Hôpital Maisonneuve-Rosemont, Queen Victoria Hospital, and Sint-Augustinus GZA Hospital, respectively). A telehealth option will be available for the participants via institutionally secured platforms.

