### Statistical Analysis

As mentioned, a power calculation was done based on a previous study [23] for the primary outcome (changes from baseline to 6 months). Every measure of facial symmetry and synkinesis will be judged by 3 assessors, blinded to group assignment. Intraclass correlation coefficients will be calculated to ensure interrater reliability, and the resulting means of the assessors’ findings will be used for further statistical analysis. We will first gather descriptive statistics to provide summary data. Then, for continuous variables (Emotrics measurements, Sunnybrook global score, FNGS 2.0 global scores, FACE score, FDI, and intrinsic motivation inventory), a mixed model analysis with patients as random variables and time+group assignment as fixed variables will be considered, with auto-regressive covariance structure, given the structure of the time points for the assessments. Comparison between the timing of recruitment after PFP onset (3-6 months after onset vs 6-9 months vs 9-12 months) and outcomes at T2 and T3 will be specifically measured using multilevel analysis. Kruskal-Wallis analyses will be considered for ordinal variables (synkinesis subscores, symmetry subscores, and motivation subscores). Finally, chi-square analysis will be considered for dichotomous variables (adherence yes or no). Data will be encoded with Excel sheets, and SPSS (IBM Corp) will probably be used for statistical analysis.

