Irrespective of the etiology and group allocation (fNMR vs mirror therapy), our hypothesis posits that all patients with peripheral facial palsy enrolled in this study will experience improvements in facial symmetry, synkinesis, and quality of life [11,23,40]. Drawing on previous studies [23,41] and considering that mirror therapy appears most beneficial when initiated early, we anticipate mirror therapy to have greater benefits for patients in the paretic phase (3-6 months after onset), particularly in terms of restoring facial symmetry. Patients presenting with synkinesis at the time of recruitment should experience a decrease in synkinesis in the fNMR group, as indicated by several previous studies [4,5,7,13,14]. Similarly, a decrease in synkinesis is expected in the mirror therapy group, but no significant differences between the 2 groups are anticipated. Moreover, in line with previous findings [5,23], we expect both the fNMR and mirror therapy groups to demonstrate improvements in self-reported quality-of-life measures. Additionally, motivation is crucial in achieving positive therapy outcomes [42] and will be specifically assessed in this study. The hypothesis of greater motivation with mirror therapy is based on a previous study where patients reported that performing facial exercises while viewing a symmetrical face aided them as it represented their desired goal [41]. On the contrary, some patients may experience emotional responses when confronted with a face they perceive as “lost” due to facial paralysis.

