### Strengths and Limitations

The primary strength of this protocol lies in its international multicentric collaboration, which will facilitate the examination of a substantial number of participants representing diverse etiologies of peripheral facial nerve palsy (n=90, with 45 patients per group). The randomized controlled trial design used in this study allows for assessing the potential additional benefits of incorporating mirror therapy into the rehabilitation of PFP. This investigation has the potential to contribute to an evidence-based approach for clinicians involved in the care of these patients.

However, the study design does have certain limitations. First, it is not feasible to blind both the patients and treating clinicians to the assigned conditions, which could introduce bias in terms of motivation and perception of treatment efficacy. To mitigate these risks, blinded judges will be involved in assessing participants, and therapists will use a standardized feedback approach in both therapy sessions and assessments. Additionally, using Emotrics will allow for more objective facial metrics at each assessment time point [33,45]. Second, the inclusion of paretic patients in the study poses a potential confounding factor due to the occurrence of spontaneous recovery in certain cases of facial palsy [3]. However, the large number of participants and their enrollment at least 3 months after the onset of symptoms should help mitigate potential biases. It is worth noting that in Bell palsy, the most common cause of PFP, approximately 70% of patients experience full recovery within 3 months of onset [3]. The advantage of including patients across such a broad timeframe (3-12 months after onset) is to recruit a cohort that is as representative as possible of the clinical reality of facial rehabilitation in different countries.

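### The phase analysis compares outcomes between phases, but the stated hypothesis needs a group×phase contrast

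*Protocol article*

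**What the plan says.** The abstract's Objective paragraph sets the main aim as to "compare the efficacy of an added mirror therapy component with fNMR in patients with peripheral facial palsy (PFP) sequelae in 3 different stages". It then lists effects of combined therapy versus fNMR alone, the last item being "4) different stages of facial palsies". In the Discussion (Comparison With Prior Work) the hypothesis has a direction: "we anticipate mirror therapy to have greater benefits for patients in the paretic phase (3-6 months after onset". The Conclusions section returns to which modalities work better at which stage. The Study Aims section in the main text, however, stops at its third objective: "3) to measure the effects of combined therapy versus fNMR alone on motivation and treatment adherence".

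Under Statistical Analysis, the one analysis that involves phase is "Comparison between the timing of recruitment after PFP onset (3-6 months after onset vs 6-9 months vs 9-12 months) and outcomes" at T2 and T3, by multilevel analysis. The mixed model for continuous outcomes has time and group as fixed effects and patient as random effect.

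Recruitment and Compensation sets quotas of 30 patients in each of three phases and continues: "They will then be randomized into 2 groups, mirror therapy plus fNMR or fNMR alone, by computerized block randomization". Strengths and Limitations states that "the inclusion of paretic patients in the study poses a potential confounding factor due to the occurrence of spontaneous recovery".

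**The concern.** A larger benefit of mirror therapy in one phase is a statement about effect modification: the difference between arms is itself different across phases. The analysis described sets phase against outcome, so what it estimates is how patients recruited at different times fare, whichever treatment they had. Paretic patients may do better in both arms because some are still recovering spontaneously. That result would say nothing about mirror therapy, yet it is the only phase result the stated plan is sure to produce. The abstract's fourth objective would then have no analysis that answers it.

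**Working it through.** **1. What the stated comparison estimates.** Let μ_P and μ_R be the mean outcomes under fNMR alone for paretic patients and for the other two phases combined. Let δ_P and δ_R be the effects of adding mirror therapy in each. With 1:1 allocation, half of each phase receives mirror therapy, so:

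- phase comparison, arms pooled: (μ_P − μ_R) + (δ_P − δ_R)/2
- group×phase contrast: δ_P − δ_R

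The first mixes prognosis with half of the effect modification and cannot separate them. For example, δ_P = 0.6 SD with δ_R = 0 moves the phase comparison by 0.6/2 = 0.3 SD. A purely prognostic advantage of 0.3 SD, with no treatment effect anywhere, moves it by the same amount. The time+group model has no phase term, so it does not help.

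**2. The plan's own sample size.** Inputs from Recruitment and Compensation: power 0.8, effect size 0.6 (taken here as a standardised mean difference, an assumption), α printed as .005, N = 90. The formula is n per arm = 2(z_α/2 + z_0.8)²/d².

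- α=.05 two-sided: 2(1.960 + 0.842)²/0.36 = 43.6, so 44 per arm, N = 88 (t-test: 45 per arm, N = 90).
- α=.005 two-sided: 2(2.807 + 0.842)²/0.36 = 74.0, so 74 per arm, N = 148.

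The 90 reproduces at .05 and not at the printed .005. That discrepancy is a separate matter. Here it shows only that 90 fits the overall two-arm comparison, so .05 is used below, with .005 given for range.

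**3. What a group×phase analysis could detect.** Thirty patients per phase gives about 15 per arm, assuming complete follow-up.

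- Within one phase: SE = √(2/15) = 0.365 SD. Power for d = 0.6 is Φ(0.6/0.365 − 1.960) = 0.38, or 0.35 by t-test (0.10 at α=.005). A t-test reaches 80% power at d = 1.06. The 95% confidence interval half-width is about 1.96 × 0.365 = 0.72 SD.
- Paretic versus the rest: SE = √(2/15 + 2/30) = 0.447 SD. The contrast detectable with 80% power is (1.960 + 0.842) × 0.447 = 1.25 SD (1.63 SD at α=.005). Power for a contrast of 0.6 SD is 0.27 (0.07 at α=.005).
- Two-degree-of-freedom interaction test, phase effects 0.6/0/0 SD, 84 error df: power 0.20.

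**4. How much stratification matters.** Suppose, as an assumption, that allocation is 45:45 overall and ignores phase. The number treated within a phase is then hypergeometric (30 drawn from 90, 45 of them treated). The probability of an 18:12 split or worse is 0.26 in a given phase, and 0.50 (by simulation) in at least one of the three. The relative standard error within the phase is √(1/18 + 1/12)/√(2/15) = 1.02 at 18:12, and √(1/20 + 1/10)/√(2/15) = 1.06 at 20:10. Imbalance is fairly likely and costs little.

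**The case against.** The strongest reply is that the sentence is underspecified, not wrong. It says multilevel analysis and lists no terms, a fuller analysis plan may include group, and the article elsewhere frames the stage question as mirror therapy against fNMR. It is also true that Study Aims omits the stage objective, that the sample size rests on the overall 6-month change, and that the abstract's Results paragraph says only that a paretic benefit could be noted. What stands is that stage is not presented as a powered claim. What does not stand is the defence of the wording: the sentence names the two things to be compared, and treatment is not one of them. Multilevel describes how clustering is handled and does not supply a group×phase term.

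Three stronger readings are tempting, and the documents do not support them. First, a reader might infer that randomisation is unstratified. The article is silent on strata, phase quotas followed by blocks fit either scheme, and an article may leave this to the full protocol. Second, a reader might infer that without stratification the trial could not address phase at all. Phase is a baseline variable, so within-phase comparisons remain randomised and the interaction remains estimable. Chance imbalance affects precision and is not a bias. Third, a reader might infer that the authors would present better paretic outcomes in both arms as efficacy. They expect improvement in both arms and name spontaneous recovery as a confounder, so that intention cannot be attributed to them.

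**Conclusion.** The point holds as a mismatch between question and analysis. The abstract's fourth objective and the directional hypothesis in the Discussion concern effect modification by phase, while the described analysis gives a prognostic comparison of phases. The data would allow the right contrast; the plan as worded does not produce it.

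The power figures in the working do not measure this defect. They follow from N = 90 and stay the same after the correction. They show why the corrected analysis has to be called exploratory: it can give estimates with wide intervals, and it is unlikely to establish in which phase mirror therapy helps. They rest on a standardised effect of 0.6, two-sided α=.05, 1:1 allocation within phase and no dropout. Loss to follow-up or α=.005 would make them worse.

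**What to change.** - In Statistical Analysis, replace the phase-outcome comparison with a group×phase (or group×months since onset) interaction at T2 and T3, adjusted for the baseline value. Report three phase-specific group differences with confidence intervals beside the interaction estimate.
- Label this analysis exploratory, citing about 15 patients per arm per phase, and word the stage objective and hypothesis to match.
- Add phase as a covariate to the primary model, since it is expected to be prognostic.
- Make the abstract's objectives and Study Aims agree on whether stage is an objective.
- State whether the blocks are stratified by phase. If they are not, stratify them as a secondary gain in precision.

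The cost is wording and, if stratification is added, setting up the randomisation list. No extra patients or visits are needed. The analysis wording should be settled before outcome data are seen, and stratification can only be introduced before enrolment.

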### Measures

For data collection, each measure will be taken at baseline, 3 months, 6 months, and 1-year postintervention. Evaluation sessions will be recorded, allowing 3 independent evaluators to blindly assess the objective outcome measures. The final assessment (T3) will measure the training retention of participants following therapy sessions.

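### The synkinesis and other ordinal subscores are assigned only a Kruskal-Wallis test, so synkinesis as an outcome of its own gets no longitudinal or baseline-adjusted analysis

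*Protocol article*

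**What the plan says.** Under Statistical Analysis, the outcomes are split by variable type. The plan specifies "for continuous variables (Emotrics measurements, Sunnybrook global score, FNGS 2.0 global scores, FACE score, FDI, and intrinsic motivation inventory), a mixed model analysis". In that model the patient is the random effect, the fixed effects are time and group, and the covariance is autoregressive. For the subscores it says only that "Kruskal-Wallis analyses will be considered for ordinal variables (synkinesis subscores, symmetry subscores, and motivation subscores"). The article does not say which response enters that test (a visit value, a change or several visits), nor which groups it compares. The abstract is firmer than the section itself: there the Kruskal-Wallis analyses are listed among those that will be carried out.

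The design around this test is stated. Under Measures, "each measure will be taken at baseline, 3 months, 6 months, and 1-year postintervention". There are two arms: "They will then be randomized into 2 groups, mirror therapy plus fNMR or fNMR alone, by computerized block randomization". The power calculation is described as being "for the primary outcome (changes from baseline to 6 months"). The first specific objective under Study Aims is "to measure the effects of combined therapy compared to fNMR alone on" facial symmetry and facial synkinesis. For the rated outcomes, "Intraclass correlation coefficients will be calculated to ensure interrater reliability", and the mean of the three assessors is what gets analysed.

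**The concern.** Kruskal-Wallis compares independent groups on one value per patient. It has no place for a covariate and no within-patient structure. The same section recognises the repeated design for the global scores, giving them a patient effect and a serial covariance, but gives the subscores nothing equivalent.

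This matters most for synkinesis. Symmetry is also measured by Emotrics and is part of the global scores, all of which go to the mixed model. Synkinesis reaches the mixed model only inside composite scores. As an outcome in its own right it is left to the rank test.

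The Discussion expects synkinesis to fall in both arms without a significant difference between them. A non-significant rank test cannot support that expectation. A precise estimate of the difference with a confidence interval is needed, so giving up precision on this outcome has a real cost.

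**Working it through.** **What the test can use.** With k groups of sizes n_j, rank sums R_j and N patients in total, H = 12/[N(N+1)] · Σ R_j²/n_j − 3(N+1), apart from the correction for ties. With k = 2 this is the square of the standardised Wilcoxon rank-sum statistic. Only the ranks of one response enter. No term carries the baseline subscore or links the visits of a patient.

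**Why adjustment helps.** Take a continuous score with SD 1 at both visits and correlation r between baseline and 6 months. The variance of the response being compared is:
- 6-month value: 1
- change from baseline: 2(1 − r)
- baseline-adjusted value: 1 − r²

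At r = 0.09 these are 1, 1.82 and 0.99. At r = 0.8 they are 1, 0.40 and 0.36. Adjustment is never worse than either alternative. Change is worse than ignoring baseline when r is below 0.5.

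**Simulation inputs.** From the article: 45 patients per arm, four visits, and a shift of 0.6 SD (the effect size under Recruitment and Compensation), applied at every post-baseline visit. Assumed, because the article does not give them: a 5-level score cut from a normal variable, correlation ρ of 0.3 to 0.8 (autoregressive or exchangeable), a 5% level and no dropout. There were 2,000 runs without an effect and 1,000 with one per setting. The baseline-adjusted comparator regresses the 6-month ranks on the baseline ranks and compares the residuals between arms. Under the autoregressive structure the correlation between baseline and 6 months is ρ², since they are two visits apart: 0.09, 0.25, 0.49 and 0.64.

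The article gives no figure for the power of the subscore tests, so there is none to reproduce.

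**Power at a 0.6 SD shift**

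| ρ, structure | Kruskal-Wallis, 6-month value | Kruskal-Wallis, change to 6 months | Baseline-adjusted ranks |
|---|---|---|---|
| 0.3 autoregressive | 0.752 | 0.480 | 0.751 |
| 0.3 exchangeable | 0.774 | 0.615 | 0.803 |
| 0.5 autoregressive | 0.747 | 0.582 | 0.773 |
| 0.5 exchangeable | 0.748 | 0.692 | 0.824 |
| 0.7 autoregressive | 0.763 | 0.690 | 0.849 |
| 0.7 exchangeable | 0.746 | 0.877 | 0.927 |
| 0.8 autoregressive | 0.759 | 0.834 | 0.897 |
| 0.8 exchangeable | 0.749 | 0.959 | 0.980 |

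Against the adjusted analysis, the 6-month value loses between nothing (0.752 against 0.751) and 23 points (0.980 − 0.749 = 0.231). The change score loses between 2 points (0.980 − 0.959 = 0.021) and 27 points (0.751 − 0.480 = 0.271).

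**Type I error at a nominal 5%.** The 6-month value gave 4.2–6.0%, change 4.3–5.7%, and adjusted ranks 4.2–5.6%. All three are valid.

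**Two hypothetical uses that the article does not announce.** Pooling all four visits as independent values gave 10–27%. Treating the four visits as the groups, with no true change over time, rejected in 2.1% of runs at correlation 0.3 and in 0.4% or fewer from 0.5 upwards, so that test is strongly conservative.

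**The case against.** The strongest reply is that the article fixes little here. The method is only to be considered, and a condensed article may leave the response and the visit to the full plan. That is fair as to those details, and their absence is not the point. What stands is that the one method named for the subscores is of a kind that cannot adjust for baseline or combine visits, whichever response is chosen, and the abstract says that it will be used.

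Several stronger readings are tempting and are not supported:
- **That the test ignores baseline altogether.** The article frames its primary outcome as change to 6 months. Applied to that change, the test does use baseline and keeps its size.
- **That false positives will be inflated.** This needs visits to be pooled as if independent, and nothing in the article says so.
- **That all of objective 1 rests on this test.** Symmetry is also covered by Emotrics and the global scores. The FNGS 2.0 global score includes synkinesis. The gap is synkinesis as a separate outcome.
- **That the global-score model could simply be copied.** As written it has time and group only. It states neither a group×visit term nor a baseline covariate.

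The groups might also be the three onset periods, which the preceding sentence discusses and which would suit a test for three or more groups. This cannot be excluded, but then the section would name no comparison of the arms on the subscores at all.

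Some smaller points on the other side also stand. A baseline-adjusted analysis at 6 months alone also drops patients who miss that visit. A rank test can be accompanied by an estimate with a confidence interval, such as Hodges-Lehmann. Means of three ratings may stay skewed and bounded, so a rank method remains defensible as a check.

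**Conclusion.** The point holds as a poor match between method and design, not as an invalid analysis. The subscores are measured four times but are assigned only an independent-groups rank test. As a result, synkinesis is never analysed as its own outcome by a longitudinal or baseline-adjusted method.

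Under the assumptions above, the cost is a power of 75–77% (6-month value) or 48–96% (change), against 75–98% with baseline adjustment. The loss is close to zero for the 6-month value at low correlation, and for change at high correlation. It exceeds 20 points at the opposite ends.

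The sizes depend on the assumed number of levels, cut-points and correlations, none of which is in the article. They also depend on the 5% level, whereas the power statement gives .005. Only the baseline-adjusted rank analysis was simulated; the repeated-measures ordinal model was not. The direction of the result follows from the variance formulas and does not depend on the particular cut-points.

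**What to change.** Replace Kruskal-Wallis as the main analysis of the synkinesis, symmetry and motivation subscores by one of these:
- a repeated-measures ordinal model (cumulative-logit mixed model or GEE) for the 3-, 6- and 12-month subscores, with group, visit, group×visit and the baseline subscore; or
- a baseline-adjusted rank analysis at 6 months, if a simpler method is preferred.

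Write these terms out in full instead of referring to the global-score model, which does not contain them. Report the 6-month difference between arms with a confidence interval. Keep the rank test of change to 6 months as a sensitivity check, and state its response and groups.

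The cost is a change of wording and slightly more modelling work. No extra data are needed, because every measure is already planned at all four visits.

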### Study Procedures

This trial will compare the effect of mirror therapy in addition to gold standard fNMR (experimental group) over fNMR alone (control group) in patients with peripheral facial palsy dealing with sequelae 3-12 months after onset. During 6 therapy sessions (Textbox 1), all patients will benefit from standardized education on facial anatomy and physiology, eye care, and management of facial dysfunction (eg, eating, drinking, speaking, and nonverbal communication), as well as from rehabilitation to increase symmetry and decrease synkinesis, specific to their needs. These sessions will be provided by speech-language, physical, or occupational therapists, all certified by their respective professional corporation. In addition, a minimum of 5 years of expertise in facial palsy training is required to be included in the study. These clinicians will also perform the different study measurements, but 3 judges (also experts in facial therapy but blinded to therapy allocation) will then analyze the data. The mirror therapy group will also receive modified visual feedback during facial retraining, along with appropriate instructions about its use. In parallel, patients will be prescribed daily specific at-home rehabilitation depending on the nature of their group. Patients in the combined group (mirror therapy plus fNMR) will do their therapy at home with the MEPP 2.0 app [31], while patients in the fNMR group alone will do their therapy at home with the Physitrack app [32]. Figure 2 presents the overall study design.

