**Figure 2 figure2:**
[figure not shown]
Overall study design. Participants in the control group and in the experimental group are assessed at baseline (T0), 3 months postintervention (T1), 6 months postintervention (T2), and 12 months postintervention (T3). fNMR: facial neuromuscular retraining.

Frequency and length of appointment.SessionsSession 1 (1 hour to 1 hour and 30 minutes) for initial assessment and start of management.Session 2 (1 hour) 1 month after session 1.Session 3 (1 hour) 1 month after session 2.Session 4 (1 hour) generally 1-2 months after session 3.Session 5 (1 hour) is generally 3 months after session 4.Session 6 (1 hour) final session generally 6 months after session 5, then discharge to continue independently.The total treatment course will last 12 months.2-3 sessions of 10 to 15 minutes of daily home rehabilitation are expected to be done by the patients from baseline until 12 months.

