### Motivation and Adherence to Treatment

To measure the effects of combined therapy compared to fNMR alone on the rehabilitation process of the participants and motivation to treatment, the intrinsic motivation inventory [37] will be used. This multidimensional tool has been developed to assess participants’ intrinsic motivation toward specific activities in laboratory experiments. Interest or enjoyment, perceived competence, effort, pressure or tension, usefulness, perceived choice, and relatedness of a task are all assessed while the participant performs a specific task. The scale has been validated in several contexts [37,38]. Patients’ compliance to treatment will be assessed through intrinsic features of both websites that record metadata every time the participant logs in. These features allow therapists to see if the patient completed their rehabilitation program as recommended. Figure 3 shows an example of the metadata that the MEPP website can generate on an Excel (Microsoft Corp) sheet about compliance with treatment.

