Finally, we anticipate that patients in the mirror therapy group will exhibit better treatment adherence compared to those undergoing fNMR alone. Adherence to facial retraining has been shown to be influenced by various factors, including time constraints due to other daily activities and accessibility to the training facilities [43]. Facial therapists often overestimate their patients’ commitment to the facial rehabilitation process, with data indicating that only 30% of patients fully comply [43]. Nonadherence to therapy can impact treatment outcomes, highlighting the importance of measuring adherence in this study. Objective measures of adherence using metadata will be used, providing strength compared to relying solely on subjective measures of compliance. Subjective measures of compliance (such as patient questioning) may be influenced by patients’ memory or perceptions [44]. Furthermore, the postpandemic shift toward telehealth for service delivery may facilitate adherence [44]. In this study, we will document whether participants received care via telehealth and examine whether this factor appears to influence compliance.

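### Adherence is recorded by a different app in each arm and then cut to yes/no for a chi-square test, so a recording difference cannot be told from a mirror-therapy effect and graded information is lost

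*Protocol article*

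**What the plan says.** Under Study Procedures, patients in the combined arm "will do their therapy at home with the MEPP 2.0 app", while "patients in the fNMR group alone will do their therapy at home with the Physitrack app". Under Motivation and Adherence to Treatment, compliance is read from "intrinsic features of both websites that record metadata every time the participant logs in". The next sentence adds: "These features allow therapists to see if the patient completed their rehabilitation program as recommended". The textbox on appointments gives a prescribed amount that could serve as a denominator: "2-3 sessions of 10 to 15 minutes of daily home rehabilitation are expected to be done by the patients from baseline until 12 months".

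Under Statistical Analysis, "chi-square analysis will be considered for dichotomous variables (adherence yes or no"). No other analysis of adherence between arms is named.

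Adherence is part of specific objective 3 (Study Aims). The Discussion gives the expected direction: "we anticipate that patients in the mirror therapy group will exhibit better treatment adherence". It also presents the metadata as an objective measure and therefore a strength. Strengths and Limitations covers the lack of blinding of patients and clinicians and spontaneous recovery, but not the use of two recording platforms.

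**The concern.** No patient in one arm is measured with the other arm's tool. Randomisation balances the patients but not the instrument. Suppose one app closes a session automatically and the other needs a manual confirmation, or one counts a partly finished session and the other does not. The arms would then differ in recorded adherence even if patients trained equally. The article neither equates the two records nor warns about the difference, and it relies on the metadata for its objectivity.

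The second issue is separate. Each app makes a record at every log-in over many months, against a stated daily prescription. Reducing that to one yes/no per patient costs power in a trial of 45 per arm. At stake is whether the third objective can be answered: a positive result could not be attributed to mirror therapy, and a negative one could easily reflect the coarse measure.

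**Working it through.** **Plan's own figure.** There is none to reproduce. The sample size is stated for the primary outcome only, and no power is given for adherence.

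**Inputs**
- 45 patients per arm (Strengths and Limitations).
- Control adherence 30%. The Discussion cites "data indicating that only 30% of patients fully comply" from another source. That it applies to this trial's controls and to its adherent category is an assumption.
- Two-sided α = .05, an assumption. The only α in the article (.005) belongs to the primary-outcome calculation.
- Graded adherence normal with equal spread in both arms, an assumption used only to compare cut with uncut.

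**1. Chi-square power at 45 per arm.** Power = Φ[(Δ − 1.96·SE₀)/SE₁], with SE₀ = √(2·p̄(1−p̄)/45) and SE₁ = √([p₁(1−p₁)+p₂(1−p₂)]/45).

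For 30% vs 50%: Δ = 0.20, p̄ = 0.40, SE₀ = √(2×0.24/45) = 0.1033, SE₁ = √((0.21+0.25)/45) = 0.1011. Then (0.20 − 0.2024)/0.1011 = −0.024, and power = 0.49.

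| Control | Mirror therapy | Power |
|---|---|---|
| 30% | 40% | 0.17 |
| 30% | 50% | 0.49 |
| 30% | 59% | 0.80 |

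**2. The same shift left uncut.** Moving from 30% to 50% above a fixed threshold is a shift of z(0.70) − z(0.50) = 0.524 − 0 = 0.52 SD. A two-sample t-test with 45 per arm has power 0.69 for that shift.

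**3. Information kept by the cut.** Relative efficiency = φ(c)²/[p(1−p)]. At p = 0.30, c = 0.524 and φ(c) = 0.3477, so 0.1209/0.21 = 0.58, a loss of about 42%.

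| Share adherent at the cut | Information kept |
|---|---|
| 50% | 64% |
| 30% | 58% |
| 20% | 49% |
| 10% | 34% |

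**4. What a recording difference could do.** This is an illustration only, because every error rate is assumed. Let true adherence be 30% in both arms, and let each app classify adherent patients with a given sensitivity and non-adherent ones with a given false-positive rate. Recorded share = 0.30·sensitivity + 0.70·false-positive rate.

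| App A (sens / false pos) | App B (sens / false pos) | Recorded A vs B | Chi-square rejects |
|---|---|---|---|
| 0.95 / 0.05 | 0.95 / 0.05 | 32% vs 32% | 5% |
| 0.95 / 0.05 | 0.85 / 0.05 | 32% vs 29% | 6% |
| 0.95 / 0.15 | 0.85 / 0.05 | 39% vs 29% | 17% |
| 0.95 / 0.25 | 0.85 / 0.05 | 46% vs 29% | 38% |

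A and B are deliberately not named. Either app could be the more generous one, and the false signal would then point for or against mirror therapy.

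**The case against.** Several objections have force. The apps are part of the assigned home programmes, so a true difference in use is a legitimate effect of the package; only a recording difference is an artefact, and none has been shown. Chi-square is valid for a two-arm yes/no outcome, the wording is tentative, and the threshold may sit in the full protocol, so its absence here is no fault. Adherence is not the outcome the trial was sized for, and even the uncut analysis reaches only 0.69. All of this stands. It limits the point without removing it: the article does state a yes/no comparison across two instruments, and it names neither a graded analysis nor the limitation.

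Stronger readings are tempting but unsupported:

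- A reader might infer that adherence is a bare count of log-ins. The article says that metadata are recorded at log-in and also that they show whether the programme was completed. The figure illustrating the MEPP record is not available, so the exact fields are unknown.
- A reader might infer that the cut loses most of the information. At 30% the loss is about 42%. It exceeds half only when about 20% or fewer count as adherent, and no cut-off is given.
- A reader might infer that the bias favours mirror therapy, because control patients could practise without opening Physitrack while mirror sessions need software. The article says that control patients train with the app. Off-app practice is a conjecture, and so are its amount and direction.
- A reader might want a diary ticked by patients in both arms. That would bring back the self-report which the Discussion gives as its reason for using metadata, and the fix does not need it.

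**Conclusion.** The point holds in two parts. The first rests on the text alone: arm and recording platform coincide completely, so the adherence comparison cannot distinguish mirror therapy from the way its app records sessions, and the article does not acknowledge this. The direction and size are unknown; the rejection rates of 6% to 38% above show only what assumed error rates would do.

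The second is a matter of efficiency. With 45 per arm and two-sided .05, the yes/no test has power of about 0.49 for 30% versus 50%, against about 0.69 for the same shift analysed uncut, and keeps about 58% of the information. These figures depend on the 30% rate applying to this trial's controls and on a normal model. Real adherence is a bounded proportion, so they are a guide to the order of the loss. The point should be dealt with, but it does not touch the primary outcome.

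**What to change.** 1. Define adherence identically in both arms as completed sessions divided by prescribed sessions, derived from the app metadata. Check that both exports support the same rule for a completed session; if they do not, use the finest unit that both record. The abstract describes 6 months of training and the appointment textbox a 12-month course, so these must be reconciled before the denominator's time window is set.
2. Compare that proportion or count between arms with a model that allows for overdispersion, for example a beta-binomial. Keep yes/no with chi-square as a secondary summary.
3. Add the two-platform recording to Strengths and Limitations.
4. Word the adherence conclusion as the MEPP 2.0 package versus the Physitrack package, not as mirror therapy versus none.

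The cost is slightly more analysis work, a check of the two export formats, and a narrower conclusion. Patients carry no extra burden and no new data are collected. The change does not by itself remove a recording difference between the apps; items 3 and 4 are there for that reason.
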